### **General Study Procedures.**

**Orientation Session:** After verifying eligibility and completing the informed consent process, participants will be mailed two saliva test kits. Upon receiving the saliva tests, participants will be trained in the operation of the smartphone application (“app”) used to submit breath and saliva samples remotely and will have the opportunity to practice submitting saliva samples. The first sample that subjects submit upon receiving their saliva test kits will be used to validate smoking status and subjects will be withdrawn prior to randomization if they are found to be non-smokers. Women who provide a baseline saliva test validating that they are smokers will be randomized to one of the two treatment conditions, and will be provided with information about that condition and a brief quiz (see attached) as part of their orientation session. The orientation session will be conducted by telephone. Prior to the orientation session, participants will be mailed a CO monitor, additional saliva cotinine test kits, and an instruction manual containing general information about study procedures and where to download the app that they will use during their participation, as well as specific information about how frequently they should submit breath and saliva samples and a schedule of potential earnings. Given that over 80% of pregnant women can be expected to own smartphones, these women will use their existing phone during their participation to increase the ecological validity of using a mobile phone to deliver the intervention. Women who do not own a smartphone but have access to a computer with Internet access may pursue this option instead. We will collect data on the number of participants who use mobile phones vs. computers to participate in the intervention. During the orientation session, participants will also be informed that we will cover the costs of study-related data transfer if necessary. The purpose of this is to enhance the internal validity of this efficacy study by reducing between subject variability in data coverage. We will also collect data on the number of participants who require assistance paying for data coverage. Other details covered during orientation include instructions specific to the condition to which participants are randomized (e.g., schedule for submitting breath and saliva samples, the schedule of potential earnings, and when the earnings commence). Researchers will read participants an information sheet specific to their treatment assignment (attached), which will be followed by a brief quiz (attached). The purpose of the quiz is simply to verify participant understanding of the condition to which they are randomized. Participants will respond aloud to the quiz questions over the phone and any incorrect answers will be discussed, and they will be invited to ask any additional questions upon completing the quiz. Participants will select a quit date during orientation (either the first Monday following the call or the next Monday), and research staff will contact them by phone on the Friday prior to their quit date. Staff will also inform participants to contact them in the event that their phone is lost, stolen, or broken. In sum, participants who complete the informed consent process will be mailed two saliva test kits to verify their smoking status prior to being assigned to one of the two treatment conditions. Two tests will be sent in case participants’ first sample is invalid (e.g., insufficient saliva to produce a reading) and they need to complete a second test to verify smoking status. Participants who are verified to be smokers will then complete the treatment assignment phone call, after which study staff will provide them with the equipment that they will need for the remainder of the study (e.g., breath CO monitor and additional saliva test kits).

**Mobile-Phone Based Financial Incentives:** The intervention will be delivered on participants’ smartphones via an app installed on their phone either before or during the orientation session. The process of submitting a video entails the following steps: (1) Participant opens the app, which requires them to type in a password. Their username and password (stored as a secure, “irreversible” one-way hash) will be stored in a configuration file accessible only to the application; (2) The app will verify the password and participants will be taken to the “home” screen which will show their cumulative earnings to date and a “post video” button; (3) The app will attempt to contact the server over the Internet (via a 3G/4G mobile network) to determine the correct time and status of the participant; (4) The participant will click on the post video button, thereby leading them to a simple interface for recording videos that contains a start/stop recording toggle button, a play button to review the recorded video, and a post button to send the video to the server; (5) After posting the video, the server will display a voucher based on the voucher schedule cached from the prior video upload. The app will then create a text file containing a timestamp and video file. These files will be archived, compressed, and encrypted to prevent tampering and/or eavesdropping while in transit. The app will maintain a file lock on the video until it is discarded

or posted to prevent participants from tampering with their videos; (6) If a 3G/4G or WiFi Internet connection is available, the app will poll connection status in the background until an upload can be initiated; (7) When the server receives the upload, the video will be extracted and the content registered with the system; (8) A text message verifying that the video was received will be sent to the participant and their account will be updated; (9) Research staff will review and validate videos (see Validating Videos below). Participants will be able to check their recent and cumulative earnings on a mobile-friendly site. These same steps will be employed among participants using the computer-based treatment delivery platform. The app for use in the current study will be designed by DynamiCare Health, Inc. upon receiving the grant award. [name] (Co-Founder/CEO) at DynamiCare Health has received specifications for the design of the app that are identical to what we describe above, and will modify their existing treatment delivery platform to be consistent with these specifications.

**Abstinence Criterion:** Consistent with our current ongoing clinical trial (CHRMS 13-143), participants will receive incentives during week 1 for all breath CO samples where  $\text{CO} \leq 6$  ppm. Breath CO has a relatively short half-life, thus twice daily CO testing during week 1 will help detect recent smoking. This frequency of testing also offers the advantage of allowing women to obtain frequent access to reinforcement thereby engaging them early in the intervention. Although recent studies to promote smoking cessation among pregnant women have employed cut points as high as 10 ppm^87, existing data and our group's experience suggest that moderate levels of smoking can go undetected when using higher cut points. After week 1, incentives will be based on salivary cotinine levels. Salivary cotinine has a longer half-life and thus is more appropriate for the less frequent schedule of routine smoking monitoring that will ensue following week 1. The test itself simply displays a positive or negative, however the equipment specifications indicate that salivary cotinine  $\geq 30$  ng/mL will register as positive which is consistent with the cut point used in prior research conducted by our group.

Participants will be informed during their orientation session about environmental sources that could elevate breath CO, as well as other sources of nicotine that could elevate salivary cotinine. Specifically, research staff will inform participants that they should avoid second-hand or environmental smoke, as well as smoking other combustible tobacco products and/or using marijuana. Thus CO readings above 6 ppm will always be considered positive during week 1 of treatment (described subsequently). Similarly, participants will be informed that other sources of nicotine (e.g., e-cigarettes, nicotine replacement therapy) may result in positive saliva cotinine tests which may prevent them from earning incentives from week 2 onwards.

**Smoking Monitoring:** We currently plan to use the iCO™ Smokerlyzer® (coVita, Inc.), a handheld Smartphone-compatible CO monitor that connects to the phone using the earphone connector, to monitor smoking status during week 1. Although the iCO™ Smokerlyzer® readings can be viewed using the iCO Smokerlyzer® app that is freely available at both the Apple iOS App Store and Google Play Android App Store, we will interface the monitor with our own customized app to permit researchers to validate that breath CO samples are submitted by the intended participants who are enrolled in the study. The iCO™ Smokerlyzer® permits a concentration range of 0-100 ppm and sensitivity results in individual 1 ppm increments. The operating life is approximately 200 tests or 3 years (whichever comes first), which will be adequate for the proposed study. Following week 1, we will use Alere iScreen OFD Oral Cotinine Screening tests to monitor smoking status via saliva cotinine testing. Salivary cotinine has a longer half-life than breath CO, making it a more appropriate measure with less frequent testing. Subjects will submit videos of themselves completing the tests, with each test taking approximately 5 minutes (i.e., 2-3 minutes of swabbing the mouth and tongue, and up to 3 minutes to produce a result). The display indicates whether the sample is either positive or negative, with a positive test registering for salivary cotinine levels  $\geq 30$  ng/mL.

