[PATH] reported owning a smartphone). Exclusion criteria include: (a) current or prior mental or medical condition that may interfere with study participation (assessed via self-report during formal intake assessment completed online or by phone using a medical and psychosocial history questionnaire), (b) smoke marijuana more than once each week and not willing to quit (marijuana smoking can inflate breath CO), (c) exposed to unavoidable occupational sources of CO (e.g., car mechanic), (d) report currently receiving opioid maintenance therapy (e.g., methadone, buprenorphine). Women who meet the inclusion criteria and complete the informed consent process will be considered formally enrolled and will be mailed equipment to participate in the study, but will not be randomized until they (1) confirm receipt of their equipment, (2) complete an orientation session on the smartphone app used in the current study (described subsequently), and (3) provide a saliva sample indicating current smoking (i.e., test strip returns a positive for cotinine, a metabolite of nicotine). Upon completing these steps, women will be randomized to either the incentives or best practices treatment condition (See Treatment Conditions). The only criteria for withdrawing participants after randomization occurs will be pregnancy termination or fetal demise.

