Women will be free to withdraw at any point during the course of the study without penalty. That will be explained during informed consent. In terms of data analysis, we will adhere to an intent-to-treat approach (Armitage, 1983) wherein all women randomized to the study conditions will be included in the analyses independent of early dropout, noncompliance, etc., with the exception of excluding women for abortion/fetal demise as is convention in this research area. Women who receive their equipment and fail to complete an orientation session, as well as women who provide a baseline CO sample indicating that they are non-smokers, will be withdrawn prior to randomization and thus not included in an intent-to-treat analysis.

**Sources of Materials:** Identify sources of research material obtained from individually identifiable human subjects in the form of specimens, records or data. Indicate whether the material or data will be obtained specifically for research purposes or whether use will be made of existing specimens, records or data.

The research materials to be obtained include interviews, questionnaires, breath and saliva specimens to verify smoking status (and serve as the basis for reinforcement in the incentives condition), and medical records to assess birth outcomes. Materials will be collected remotely using a combination of phone calls with participants, online surveys, and remote video capture via smartphone app (i.e., for submission of breath CO samples and salivary cotinine samples). Delivery reports will be obtained via fax and entered into databases with no identifying information (i.e., with subject ID only). These databases are stored on password-protected external hard drives in locked offices in a locked clinic accessible only to the PI and research staff.

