**Not applicable**

Pregnant women and their infants to develop more effective interventions to help them quit smoking and to examine improvements in birth outcomes from doing so.

**Number of Subjects:** What is the anticipated number of subjects to be enrolled at UVM/UVM Medical Center and in the case of a multi-center study, with UVM/UVM Medical Center as the lead, the total number of subjects for the entire study.

152 women and their infants in the main trial plus 60 AI/AN women and their infants recruited at a different site (ANTHC, Anchorage, AK) = 424 subjects total.

**Inclusion/Exclusion Criteria:** Eligibility and ineligibility criteria should be specific. Describe how eligibility will be determined and by whom. Changes to the eligibility criteria at a later phase of the research have the potential to invalidate the research.

A total of 152 Mom's will be recruited for the main trial plus 60 AI/AN women recruited at our collaborating site (ANTHC, Anchorage, AK). Participants will be healthy, socioeconomically disadvantaged (i.e., Medicaid insured) pregnant smokers. The inclusion criteria include: (a)  $\geq 18$  years of age, (b) report being smokers at the time they learned of the current pregnancy, (c) report smoking in the 7 days prior to completing their phone eligibility screening, (c)  $\leq 25$  weeks pregnant, (d) speak English, (e) own a smartphone (Android or iOS; 81.8% of pregnant women in wave 1 [2013-2014] of the Population Assessment of Tobacco and Health [PATH] reported owning a smartphone). The exclusion criteria include: (a) current or prior mental or medical condition that may interfere with study participation, (b) smoke marijuana more than once each week and not willing to quit (marijuana smoking can inflate breath CO), (c) exposed to unavoidable occupational sources of CO (e.g., car mechanic), and (d) currently maintained on opioid maintenance therapy. The only criteria for withdrawing someone from the trial following randomization to treatment condition will be pregnancy termination or fetal demise. Women who fail to complete an orientation session or provide an initial CO sample indicating that they are smokers will be withdrawn prior to randomization. Criteria will be assessed during a phone screen to determine preliminary eligibility and further evaluated during the formal intake assessment.

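### The protocol gives incompatible orders for mailing, orientation and randomisation, and one combination lets exclusion from the intent-to-treat set depend on the arm

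*Protocol*

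**What the plan says.** Four places in the protocol describe the steps between consent and randomisation.

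- **Participants (Methods and Procedures).** Consented women count as formally enrolled, but they "will not be randomized until they (1) confirm receipt of their equipment, (2) complete an orientation session on the smartphone app" and give a saliva sample positive for cotinine.
- **General Study Procedures, Orientation Session.** Two saliva kits are mailed after consent. A woman whose baseline saliva test is positive is randomised, and she receives information on her condition and a quiz as part of orientation. The same paragraph then says: "Prior to the orientation session, participants will be mailed a CO monitor, additional saliva cotinine test kits, and an instruction manual". That manual contains "specific information about how frequently they should submit breath and saliva samples and a schedule of potential earnings". A little later, orientation is said to cover "instructions specific to the condition to which participants are randomized (e.g., schedule for submitting breath and saliva samples, the schedule of potential earnings" and the start of earnings. The closing summary has two saliva kits first, then verification, then a treatment assignment call, "after which study staff will provide them with the equipment that they will need for the remainder of the study", with the CO monitor and further saliva kits as examples.
- **Withdrawal Procedures.** "Women who receive their equipment and fail to complete an orientation session, as well as women who provide a baseline CO sample" showing that they do not smoke are withdrawn before randomisation and are not part of the intent-to-treat analysis.
- **Inclusion/Exclusion Criteria.** "Women who fail to complete an orientation session or provide an initial CO sample indicating that they are smokers" are withdrawn before randomisation.

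Participants and Inclusion/Exclusion Criteria also allow only one ground for withdrawal after randomisation: pregnancy termination or fetal demise.

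**The concern.** Who belongs to the intent-to-treat set depends on the moment at which a woman becomes randomised, and the protocol does not fix that moment consistently. The difficulty is that the word orientation does two jobs. It is app training that must be finished before randomisation, and it is also the session in which the woman hears her arm, is read the matching information sheet and takes the quiz.

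If both uses are kept, non-completion of orientation can happen after the arm is known and still be classed as a loss before randomisation. The two arms give unequal reasons to stay on the line. Both pay for assessments and offer up to 65 US dollars for quit-line counselling, but only the incentives arm adds up to about 1,620 US dollars for abstinence. Losses at this point could therefore differ by arm. An analysis that starts from women classed as randomised would not include them, so the intent-to-treat rule would give no protection.

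**Working it through.** The finding rests on comparing passages; the arithmetic at the end only illustrates a possible size.

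**Step 1: the orders side by side**

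| Source | Before randomisation | After randomisation |
|---|---|---|
| Participants | Equipment received, orientation completed, positive saliva sample | Treatment condition |
| Orientation Session, opening | Two saliva kits, app training, positive saliva test | Condition information and quiz, within orientation |
| Orientation Session, mailing sentence | Not stated; the CO monitor, further kits and manual are mailed before orientation | Not stated |
| Orientation Session, closing summary | Two saliva kits, positive saliva test | CO monitor and further kits, following the assignment call |
| Withdrawal Procedures | Equipment received, orientation completed, baseline CO sample | Intent-to-treat follow-up |
| Inclusion/Exclusion Criteria | Orientation completed, initial CO sample | Withdrawal only for pregnancy loss |

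**Step 2: what cannot all be true**

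1. Under Participants, orientation precedes randomisation. Under the opening of the Orientation Session text, part of orientation follows it, because condition information cannot be given before an assignment exists.
2. The monitor is mailed before orientation in one sentence and supplied after the assignment call in the closing summary. If orientation precedes randomisation, as Participants says, the mailing sentence also puts sampling and earnings schedules in the post before randomisation. The same paragraph treats those schedules as condition-specific.
3. Baseline verification is by saliva in Participants and Orientation Session, but by CO in Withdrawal Procedures and Inclusion/Exclusion Criteria. A baseline CO sample needs the monitor, which the closing summary does not supply until later.

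**Step 3: one woman, two classifications**

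Suppose a woman has a positive saliva test, is assigned to Best Practices, hears this on the call and hangs up before the quiz. Under Orientation Session she has been randomised and belongs in the intent-to-treat set. Under Withdrawal Procedures she has not completed orientation, so she was withdrawn before randomisation and does not belong in it. Both rules are current text.

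**Step 4: illustration of size**

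Inputs from Sample Size Justification: 76 per arm; 40% vs 10% in late pregnancy; 20% vs 5% at 24 weeks postpartum; two-sided 0.05; chi-square test. Assumption not in the protocol: a share d = 10% or 20% of control women is lost in this way, with 76 per arm still analysed.

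Power = Φ[(|p1 − p2| − 1.96·√(2p̄(1 − p̄)/n)) / √((p1(1 − p1) + p2(1 − p2))/n)], where p̄ is the mean of p1 and p2.

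The plan's own case, 20% vs 5%: (0.15 − 1.96 × 0.0537)/0.0523 = 0.86, so power is 80.5%. This agrees with the stated figure of at least 80%.

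If none of the lost women would have quit, the observed control rate is p/(1 − d):

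| d | 24-week control rate | Power vs 20% | Late-pregnancy control rate | Power vs 40% |
|---|---|---|---|---|
| 0% | 5% | 80.5% | 10% | 99.3% |
| 10% | 0.05/0.9 = 5.6% | 76.6% | 0.10/0.9 = 11.1% | between the other two rows |
| 20% | 0.05/0.8 = 6.25% | 71.3% | 0.10/0.8 = 12.5% | 97.7% |

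If the lost women would instead have quit at twice the control rate, the late-pregnancy control rate becomes (0.10 − 0.20d)/(1 − d): 0.08/0.9 = 8.9% or 0.06/0.8 = 7.5%. The effect would then be overstated. The sign depends on who leaves, which the protocol gives no means of knowing.

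**The case against.** The strongest reply is that the inconsistency is one of wording and that a coherent order is already in the text. The opening and the closing summary of the Orientation Session agree: two saliva kits, a positive test, randomisation, then the rest. The mailing sentence can be made to fit, because the further kits and the manual could be posted after randomisation and before the telephone session. This is a fair reading of that paragraph taken alone. It does not fit Participants, Withdrawal Procedures or Inclusion/Exclusion Criteria, all of which place orientation before randomisation.

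A reader might infer something stronger from the mailing sentence: that the arm is fixed and known before smoking is verified, so that allocation is not concealed. The documents do not support this. Both Participants and Orientation Session place randomisation after the positive saliva sample, so neither order has an assignment before that test. The manual is not said to come in arm-specific versions; it could be generic and describe both conditions.

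A reader might also infer that control women are shown earnings that they cannot obtain and are discouraged by it. That is weak as well. Under Consent Procedures every woman already hears about each condition and the equal chance of assignment, and under Payment for participation control women have earnings of their own.

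Nor does the protocol imply that women lost before randomisation go unrecorded. They are formally enrolled once they consent, and Aim 2 assesses enrolment and retention. What they are outside is the intent-to-treat analysis.

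What survives all of this is Step 3: the arm is disclosed in a session whose non-completion is defined as a loss before randomisation.

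**Conclusion.** The concern holds as an internal contradiction with one real route to bias. Participants, Withdrawal Procedures and Inclusion/Exclusion Criteria cannot be followed together with the Orientation Session text, which also disagrees with itself on when the equipment goes out. If staff apply the withdrawal rule to a session in which the arm has been revealed, membership of the intent-to-treat set can depend on the arm.

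This conclusion needs only the wording of the protocol. It does not show that allocation is known early or that any woman has been excluded in this way. The loss of 10-20% is an assumption. Under it the 24-week comparison, which has almost no reserve above 80%, loses about 4 to 9 percentage points of power, while the late-pregnancy comparison hardly changes. Power is the lesser issue; the greater one is a bias whose size and direction are unknown. The point should be corrected, and it does not by itself undermine the design.

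**What to change.** Use the order of the Orientation Session closing summary everywhere.

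1. Before randomisation, send only the two saliva kits and general material that is identical for all women, without sampling or earnings schedules. Complete app training and the positive saliva test.
2. Record the assignment, and only then disclose it in the assignment call, which should have a name distinct from app orientation.
3. After that, send the monitor, the remaining kits and the condition-specific schedules.
4. Align the mailing sentence, Participants, Withdrawal Procedures and Inclusion/Exclusion Criteria with this order, including saliva rather than CO for baseline verification, since the monitor would not yet be in hand.
5. State that every woman with a recorded assignment is in the intent-to-treat set whether or not she completes the assignment call or quiz, apart from the protocol's existing exclusion for abortion or fetal demise.
6. Report the number of women lost between consent and randomisation.

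The cost is protocol wording and splitting the manual into a general and a condition-specific part; the second shipment is already described. The downside is a few days between assignment and arrival of the second pack. The protocol already offers a first or second Monday as the quit date, so the delivery time should be checked against that choice.
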